### Recruitment, randomization, and study development

Once an eligible patient is admitted to the PICU, written informed consent will be requested from parents or legal representative of the child by the physician responsible for the patient. They will be made aware that participation is voluntary, and they will be allowed to refuse further participation in the trial whenever they want.

After enrollment, the patient will be allocated randomly, in order of recruitment, into one of the three diet groups by using a randomized data table generated with EPIDAT 3.1 software (Servicio de Información sobre Saúde Pública de la Dirección Xeral de Saúde Pública de la Consellería de Sanidade, Xunta de Galicia, in collaboration with the Health Information and Analysis Unit of the Pan American Health Organization (PAHO-WHO)). A copy of the randomization list will be securely stored in an envelope located in a PICU working area desk drawer, which will be opened after patient enrollment in the study. Physicians, care givers, and investigators will know the allocation prior to the start of enteral feeding.

All patients will receive exclusively enteral nutrition via a nasogastric or transpyloric tube. The Standard Enteral Nutrition (SEN) group will be fed exclusively with cow’s milk–based infant formula (Nidina 1; Nestlé, Barcelona, Spain). The Protein-enriched Enteral Nutrition (PEN) group will be fed exclusively with a polymeric infant formula (Infatrini; Nutricia, Madrid, Spain). The High Protein-enriched Enteral Nutrition (HPEN) group will receive a polymeric infant formula (Infatrini; Nutricia) supplemented with 2.6 g of protein/100 mL of formula. The source of the protein supplement will be a non-hydrolyzed protein cow’s milk–based formula (Resource Protein Instant; Nestlé) (Table 1).

**Table 1 Tab1:** Composition of diets used in the study

	Protein (g)	Carbohydrate (g)	Lipids (g)	Energy (kcal)
Standard enteral nutrition	1.7	7.4	3.4	67
Protein-enriched enteral nutrition	2.6	10.3	5.4	100
High protein-enriched enteral nutrition	5.1	10.5	5.5	110

Content per 100 mL

Since this is an open-label trial, the assigned diet will be written down on the medical prescription of each patient and will be prepared by the PICU staff at their own unit, using for it the branded bottles where the different formulae are commercialized.

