Continuous enteral nutrition will be typically initiated within the first 24 h of PICU admission, by a transpyloric or nasogastric tube, at a rate of 0.5–1 mL/kg per hour, with increases of 0.5–1 mL/kg every 3–4 h, if well tolerated, to reach a caloric intake of 60–65 kcal/kg per day or as needed on the basis of resting energy expenditure measured by indirect calorimetry. There is no limit of time before the patient must be recruited as long as it is before the enteral feeding is initiated. The establishment of enteral nutrition should never be delayed by achieving enrollment.

Demographic data—gender, age, weight, height, and diagnosis on admission—will be recorded at inclusion. The risk of mortality at admission will be calculated by using pediatric scales: Pediatric Index of Mortality 2 (PIM2), Pediatric Risk of Mortality (PRISM), and Pediatric Logistic Organ Dysfunction (PELOD).

Blood concentrations of urea, creatinine, total proteins, albumin, prealbumin, transferrin, RBP levels, urinary concentration of urea in 24 h or isolated urine sample, and energy expenditure, oxygen consumption (VO_2_), and carbon dioxide production (VCO_2_) by indirect calorimetry (Datex S5 monitor, E-COVX; GE Healthcare/Datex-Ohmeda, Helsinki, Finland) will be measured at admission and at days 1, 3, and 5–7 after initiation of enteral feeding. Air leaks will be measured by using the mechanical ventilator. Calorimetry-derived data will be collected only in patients who meet all the following requirements: tracheal intubation, air leakage less than 10 %, fraction of inspired oxygen (FiO2) less than 80%, not treated with inhaled medicinal gases (nitric oxide, sevofluorane or heliox), and not connected to extracorporeal membrane oxygenation (ECMO). The collection of indirect calorimetry data will be carried out over 30 to 120 min.

NB will be calculated as nitrogen intake minus total nitrogen losses. Total nitrogen losses will include total urinary nitrogen and fecal/miscellaneous losses estimated in accordance with the World Health Organization recommendations [29]. Other blood biochemical parameters such as glucose, cholesterol, triglycerides, procalcitonin, C-reactive protein, ions, and blood gas will also be recorded.

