### Statistical analysis

As there are no previous studies reporting expected standard deviations, we use the standardized difference of means for computing the optimal minimum number of patients to include in the trial. The calculation of the sample size was carried out with EPIDAT 3.1 software. Given a significance level of 5% (type I error), a power of 80% (complementary of the type II error), and a minimum detectable standardized difference of means of 0.9, we need 30 patients per group (Bonferroni correction included).

We will use an intention-to-treat approach. A descriptive analysis will be performed where quantitative variables will be described by their means and standard deviations or their medians and interquartile ranges, as appropriate. The quantitative ones will be summarized by their absolute and relative frequencies. Parametric and non-parametric tests will be employed for contrasting equality among groups.

Univariate and multivariate mixed models will be used in order to assess the effects size of the different diets (fixed effects) on the patients (random effects) unadjusted and adjusted by potential confounders, respectively. *P* values under 5% will be considered statistically significant.

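### The arm is revealed at enrolment with no limit on the time to first feed, yet all post-baseline visits are counted from that feed, so unblinded staff can influence when, and whether, follow-up starts

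*Protocol article*

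**What the plan says.** All of the following is in the protocol article.

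- **Reveal.** Under Recruitment, randomization, and study development, the randomization list is kept in an envelope in a PICU desk drawer, "which will be opened after patient enrollment in the study". The same section adds: "Physicians, care givers, and investigators will know the allocation prior to the start of enteral feeding".
- **Open label.** "Since this is an open-label trial, the assigned diet will be written down on the medical prescription of each patient", and unit staff prepare the feed.
- **Enrolment window.** "There is no limit of time before the patient must be recruited as long as it is before the enteral feeding is initiated".
- **Start of feeding.** "Continuous enteral nutrition will be typically initiated within the first 24 h of PICU admission". The timing is tied to admission, not to randomization.
- **Safeguard.** "The establishment of enteral nutrition should never be delayed by achieving enrollment".
- **Visits.** In Methods, measurements are taken at admission and then "at days 1, 3, and 5–7 after initiation of enteral feeding".
- **Outcome.** Under Study outcomes, the primary outcome is the change in nitrogen balance from baseline to study ending, together with the incidence of hyperproteinemia or uremia that stops the study.
- **Analysis.** Under Statistical analysis: "We will use an intention-to-treat approach".

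**The concern.** Randomization balances the arms at the moment of allocation. Here the follow-up clock starts later, at first feed, and the staff who decide on that feed already know which formula the infant will get. Two things can then differ by arm: how far into the illness the infant is when day 1 falls, and which infants start at all.

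The protocol gives reasons why this could matter. The diets range from 1.7 to 5.1 g of protein and from 67 to 110 kcal per 100 mL (Table 1). The Background links higher protein intake to raised urea and to acidosis, so caution about starting could depend on the arm. It also places the most pronounced protein and calorie deficit in the first few days, so a shift in starting time would move the nitrogen balance measurements along a changing course. In addition, parenteral nutrition, bicarbonate infusion or renal replacement, all exclusions, could become necessary between allocation and first feed.

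If non-starters are dropped, the groups compared are no longer the randomized ones. If they are to be kept, the schedule provides no post-baseline nitrogen balance to analyse.

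**Working it through.** **Step 1: order of events.** Set side by side, the passages give: admission (baseline in Methods), consent and enrolment at any time before feeding, allocation opened and known to staff, first feed, then days 1, 3 and 5–7 counted from first feed. No interval is fixed between the allocation and the first feed. One of the listed study endings, seven days of enteral feeding, also runs from the first feed.

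**Step 2: what a non-starter contributes.** Baseline values exist. The hyperproteinemia or uremia component can be counted, and PICU discharge is a study ending that does not depend on feeding. No post-baseline nitrogen balance or serum protein value is scheduled.

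**Step 3: the plan's own sample size.** Inputs from Statistical analysis: standardized difference 0.9, alpha 5% with Bonferroni correction, power 80%, 30 per group. The number of comparisons and the sidedness are not stated; I assume three pairwise comparisons, two-sided, so alpha = 0.05/3 = 0.0167. A two-sample t test then needs 27.33, that is 28 per group, within two patients of the stated 30. At n = 30 the noncentrality is 0.9 × √(30/2) = 3.486 and power is 0.843.

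**Step 4: illustration of lost power.** The documents give no non-starter rate and state no allowance for loss, so 10% and 20% are assumptions.

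| Scenario | Per arm | Difference (SD) | Power |
|---|---|---|---|
| As planned | 30 | 0.9 | 0.843 |
| 10% lost, both compared arms | 30 × 0.9 = 27 | 0.9 | 0.794 |
| 20% lost, both compared arms | 30 × 0.8 = 24 | 0.9 | 0.734 |
| 10% lost, one arm only | 30 and 27 | 0.9 | 0.819 |
| 20% lost, one arm only | 30 and 24 | 0.9 | 0.789 |
| 10% kept, no diet effect | 30 | 0.9 × 0.9 = 0.81 | 0.747 |
| 20% kept, no diet effect | 30 | 0.9 × 0.8 = 0.72 | 0.628 |

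The last two rows need a nitrogen balance in non-starters, which the present schedule does not provide. They apply only if such values were obtained.

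**Step 5: illustration of bias.** Suppose the share q with the worst prognosis in one arm is not started and drops out, and prognosis correlates r with the outcome. For a normal prognosis score, the mean of those who remain shifts by r × φ(z_q)/(1 − q) SD, where φ is the standard normal density and z_q the q-quantile. With r from 0.3 to 1.0 (assumed):

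- q = 5%: φ/(1 − q) = 0.109, bias 0.03 to 0.11 SD
- q = 10%: 0.195, bias 0.06 to 0.20 SD
- q = 20%: 0.350, bias 0.11 to 0.35 SD

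These compare with a planned difference of 0.9 SD.

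**The case against.** **Staff must know the arm before feeding.** The formula is the intervention and the unit prepares it, so the quoted sentence is not in itself an error. This stands. The weakness is that the arm is known for an unlimited time before the decision to start; staff need the arm to prepare the feed, not to decide that this infant will be fed now.

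**The gap is probably short and partly guarded.** Entry requires enteral nutrition expected to last over 72 h, feeding typically begins within 24 h of admission, and enrolment must not delay it. Time from admission to first feed is recorded, and adjusted models are planned. These points reduce the risk. They do not close it: the no-delay rule concerns delay caused by enrolment, not delay after the arm is known, and recording the start time can reveal an imbalance but cannot restore the randomized comparison or supply missing values.

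**Handling of non-starters may be in an analysis plan that is not shown.** True, and its absence here is not part of the point. No analysis plan can change when the envelope is opened.

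**Stronger readings are not supported.** A reader might infer that every visit is timed from first feed, but Methods places baseline at admission. A reader might infer that the allocation is opened before the feed is ordered; the text says only before feeding starts. Nor does a non-starter lack all outcome data, since the safety component of the primary outcome can still be counted. Finally, nothing in the document says that staff do start or withhold feeding by arm.

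**Conclusion.** The point holds as a design weakness. Post-baseline follow-up is anchored to an event after randomization that unblinded staff can influence, with no limit on the interval, and the visit schedule does not fit the declared intention-to-treat analysis for an allocated infant who is never fed. The size is unknown. Under assumed losses of 10% to 20% in both compared arms, power for one pair falls by about 5 to 11 percentage points (0.843 to 0.794 or 0.734); at 10% it is close to the planned 80%. Selective starting is the more serious possibility, with an illustrative bias of up to 0.20 SD at 10% and 0.35 SD at 20%. All of these rest on assumed rates and correlations and on three two-sided comparisons. Because the remedy is cheap and leaves the trial open-label, the change should be made, though the article gives no evidence that harm has occurred.

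**What to change.** Amend Recruitment, randomization, and study development as follows:

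1. Take consent as early as wished, but reveal an infant's allocation only after the decision to start enteral feeding now has been made and recorded and the exclusion criteria have been re-checked, immediately before the assigned diet is written on the prescription.
2. Open each allocation individually. The article describes one list in one envelope, and once that is opened, later reveals cannot be timed in this way.
3. Do not make the reveal wait for a 24-h urine collection or for calorimetry (30 to 120 min), so that the protocol's own rule against delaying feeding is kept.
4. Reconcile two pairs of statements: the inclusion criterion, worded as if enteral feeding were already under way, with the rule that recruitment precedes feeding; and the Abstract, which puts baseline at the start of nutrition, with Methods, which puts it at admission.

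Cost: a short amendment, individually opened allocations, and access to them at whatever hour a first feed is ordered. Diets and feeding rules are unchanged. Infants who become ineligible or stop after first feed are not covered by this change.

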## Methods

### Hypothesis and aims of the study

The hypotheses of this study are that (1) critically ill infants receiving a higher amount of proteins on enteral feeding will experience a higher increase on serum protein levels—total proteins, albumin, prealbumin, transferrin, and retinol binding protein (RBP)—and NB than children receiving a standard enteral diet, (2) the administration of an enriched protein and high-protein-enriched diet does not increase energy expenditure in critically ill infants, and (3) protein-enriched and high-enriched protein enteral diets are well tolerated, and mild gastrointestinal side effects and tolerable serum urea and total protein elevation are adverse events.

The corresponding objectives are (1) to analyze whether the administration of a higher amount of protein on enteral diet improves protein metabolism observed by the increase of specific serum protein levels (total proteins, albumin, prealbumin, transferrin, and RBP) and NB in critically ill infants, (2) to evaluate the effect of protein supplementation on energy expenditure in these patients, and (3) to register possible secondary effects of the administration of protein-enriched and high-enriched protein diet.

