**Fig. 2 Fig2:**
[figure not shown]
Flowchart for this protocol, comparing the effect over protein metabolism of three different amounts of protein delivery. *Abbreviations*: *EN* enteral nutrition, *NB* nitrogen balance, *PICU* pediatric intensive care unit.

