Time between PICU admission and the initiation of enteral nutrition, total daily enteral energy and protein delivery, intravenous albumin infused, and other treatments such as vasoactive drugs, neuromuscular blockers, sedatives and analgesic drugs, diuretics, and steroids will be registered.

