## Discussion

Current recommendations about protein prescription in critically ill children are not based on randomized controlled trial (RCT) results. Data regarding protein supplementation are lacking. Studies with small sample sizes and heterogeneous patient populations are the only source for this information. A minimum intake of protein of 1.5 g/kg per day for children admitted to the PICU [16] is the current recommendation of the ASPEN in their latest guidelines. This recommendation is supported by only a systematic review [17] and a cohort study [18].

The exact and safe amount of protein needed to avoid negative PB remains unclear. Higher protein intake has been associated with early achievement of positive NB [19–21], and higher protein delivery has been related to lower mortality and higher ventilator-free days in PICU patients [23, 24]. On the other hand, enriched protein diets have been associated with elevated serum urea nitrogen levels [19, 20, 25, 26].

This RCT is designed to obtain new data about the amount of protein needed to avoid negative PB and the amount of protein that is safe without producing secondary effects. The results of the study will be important to decide whether a protein-enriched diet will or will not be useful in critically ill infants. Moreover, the results will be clinically significant to know the exact amount of protein we can recommend for critically ill infants.

In clinical practice, there is no method that can directly evaluate the protein metabolism. On the other hand, NB and serum protein levels have been used in most previous studies to estimate an adequate protein intake. We will use NB, considering a positive NB as an indicator of protein anabolism and a negative NB as protein catabolism. Moreover, we will evaluate as an indirect indicator of a protein metabolism improvement the increase of total proteins, albumin, prealbumin, RBP, and transferrin serum levels from baseline to the study endpoint.

The main problems we will face during data collection are the possible development, in any of the groups, of side effects that recommend to stop the study and the difficulty of including enough valid patients due to problems with urine collection.

In summary, this multicenter, prospective RCT will compare the effect of three different enriched-protein diets on serum levels of proteins, nitrogen balance, and energy expenditure in critically ill infants as well as their possible secondary effects.

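### Feeding to one calorie goal leaves the PEN and SEN diets with nearly the same protein dose, so PEN vs SEN is not a protein-dose comparison and the design has two protein levels at goal, not three

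*Protocol article*

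**What the plan says.** All of this is in the protocol article.

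- **Diets** (Recruitment, randomization, and study development; Table 1). SEN is a standard infant formula. For PEN, "The Protein-enriched Enteral Nutrition (PEN) group will be fed exclusively with a polymeric infant formula". HPEN is the same base formula as PEN, "supplemented with 2.6 g of protein/100 mL of formula". Table 1 gives composition per 100 mL only.
- **Feeding rule** (same section). Feeds start and step up by volume per kg, if tolerated, "to reach a caloric intake of 60–65 kcal/kg per day or as needed on the basis of resting energy expenditure". No arm has its own calorie goal, protein target or volume rule.
- **Description of the design** (Fig. 2 caption): "comparing the effect over protein metabolism of three different amounts of protein delivery".
- **Hypotheses** (Hypothesis and aims of the study). Hypothesis 1 compares infants given more protein with infants on the standard diet. Hypothesis 2 is that "the administration of an enriched protein and high-protein-enriched diet does not increase energy expenditure in critically ill infants", so it covers PEN as well as HPEN.
- **Analysis** (Statistical analysis). Mixed models will "assess the effects size of the different diets (fixed effects) on the patients (random effects"). No pairwise contrast is named.
- **Data collected**: "total daily enteral energy and protein delivery" is registered for each patient.

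**The concern.** A diet richer in protein per mL is not richer in protein per day if it is also richer in energy and is stopped at the same calorie goal. That is the position of PEN relative to SEN: its protein and its energy per mL are both about half as high again.

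Nitrogen balance is part of the primary outcome, and nitrogen intake is a direct term in it. If PEN and SEN infants receive nearly the same protein, a null PEN vs SEN result on nitrogen balance is close to built in, yet it could be reported as evidence that moderate enrichment does not help. For Hypothesis 2, a null result on energy expenditure could be reported as showing that moderate enrichment costs no energy, when almost no protein was added per kcal. If PEN and SEN do differ early on, the difference in energy delivered is a competing explanation. Nothing in the text warns against any of these readings.

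**Working it through.** **Inputs.** Table 1, per 100 mL (protein, carbohydrate, lipid, energy): SEN 1.7 g, 7.4 g, 3.4 g, 67 kcal; PEN 2.6 g, 10.3 g, 5.4 g, 100 kcal; HPEN 5.1 g, 10.5 g, 5.5 g, 110 kcal. Goal 60–65 kcal/kg/day. Ramp: start 0.5–1 mL/kg/h, up 0.5–1 mL/kg every 3–4 h.

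**The plan's own figures.** HPEN protein from the text is 2.6 + 2.6 = 5.2 g per 100 mL against 5.1 in Table 1; the difference is immaterial below. The sample size of 30 per group (standardized difference 0.9, 80% power, Bonferroni) does not enter the argument but bears on the fix. With a two-sided α of 0.05/3 (the number of comparisons is not stated, so three is assumed), a two-sample t test needs 27.3, so 28 per group. At 30 per group its power is 0.84.

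**Step 1: protein per 100 kcal** = 100 × protein / energy.
- SEN: 100 × 1.7/67 = 2.537 g
- PEN: 100 × 2.6/100 = 2.600 g
- HPEN: 100 × 5.1/110 = 4.636 g

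**Step 2: ratios at equal energy.**

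| Contrast | Protein | Carbohydrate | Lipid | Volume |
|---|---|---|---|---|
| PEN/SEN | 1.025 | 0.93 | 1.06 | 0.67 |
| HPEN/PEN | 1.78 | 0.93 | 0.93 | 0.91 |
| HPEN/SEN | 1.83 | 0.86 | 0.99 | 0.61 |

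Rounding limits for PEN/SEN protein: (2.55/100.5)/(1.75/66.5) = 0.96 to (2.65/99.5)/(1.65/67.5) = 1.09. For HPEN/PEN they are 1.72 to 1.85; using 5.2 g for HPEN gives 1.82, inside that range.

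**Step 3: dose at goal** = goal × protein per 100 kcal / 100, at 60 and 65 kcal/kg/day.
- SEN 1.52–1.65, PEN 1.56–1.69, HPEN 2.78–3.01 g/kg/day
- PEN minus SEN: 0.0627 × 0.60 = 0.038 to 0.0627 × 0.65 = 0.041 g/kg/day
- HPEN minus PEN: 1.22–1.32 g/kg/day

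The width of the calorie band itself (65/60 = 1.083) exceeds the PEN–SEN gap. At other shared goals the doses move but the ratios do not: at an assumed 50 kcal/kg/day they are 1.27, 1.30 and 2.32; at an assumed 80 they are 2.03, 2.08 and 3.71.

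**Step 4: below goal.** At equal volume, PEN/SEN protein is 2.6/1.7 = 1.53 and energy 100/67 = 1.49. I then ran the stated ramp without interruption, from fastest (start 1, up 1 every 3 h) to slowest (start 0.5, up 0.5 every 4 h), with the rate capped at goal, and summed intake.

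| Cumulative ratio | Protein, 24 h | Energy, 24 h | Protein, 72 h | Energy, 72 h |
|---|---|---|---|---|
| PEN/SEN | 1.12–1.49 | 1.09–1.45 | 1.05–1.12 | 1.03–1.09 |
| HPEN/PEN | 1.81–1.91 | 1.02–1.07 | 1.79–1.81 | 1.00–1.02 |

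**Step 5: why this is general.** Formula protein delivered = energy delivered × protein density. So the PEN/SEN protein ratio is always 1.025 times the PEN/SEN energy ratio, whatever was delivered (for example 1.45 × 1.025 = 1.49). Either the two arms get nearly equal protein, or they differ in energy by almost as much.

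**Illustration.** Assume the effect is proportional to protein and is 0.9 SD for HPEN vs PEN. Then PEN vs SEN has 0.9 × 0.0627/2.036 = 0.028 SD. With 30 per group, power is about 5% at α = 0.05, which is the type I error rate.

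**The case against.** - **The 2.5% describes the goal state, not all delivery.** Feeds advance only if tolerated, and the alternative goal is set from each patient's measured expenditure, so arm means need not be equal. This stands: a reader might infer that PEN never gives materially more protein, and the ramp figures show otherwise. It does not rescue the contrast, because by Step 5 any extra protein arrives with nearly proportional extra energy.
- **Hypothesis 1 remains testable.** It names the standard diet as comparator, and HPEN vs SEN carries 83% more protein at equal energy. This stands. A reader might infer that only HPEN vs PEN counts and that HPEN vs SEN should be demoted. The protocol does not support that. HPEN vs PEN is cleaner because the base formula is shared, but this is a matter of degree, and replacing the stated comparator in an open-label trial recruiting since December 2016 would be a substantive change.
- **The protocol nowhere claims that PEN vs SEN isolates protein, and contrasts can be left to an analysis plan.** That is partly fair; Table 1 shows energy openly. But the caption asserts three amounts of protein delivered, and no analysis plan can create a dose gap that the feeding rule does not produce.
- **The caption and the Discussion's aim "to know the exact amount of protein we can recommend for critically ill infants" are loose wording.** Agreed. Both are minor, and three well-spaced doses could not give an exact amount either.

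**Conclusion.** The point holds for the middle arm. At any shared calorie goal PEN gives about 2.5% more protein than SEN (-4% to +9% with rounding; about 0.04 g/kg/day at 60–65 kcal/kg/day). Below goal it gives up to about 1.5 times the protein over 24 h, with up to about 1.45 times the energy. PEN vs SEN is therefore a comparison of formula and energy density at every stage. At goal the trial has two protein levels, about 1.5–1.7 (SEN, PEN) and 2.8–3.0 g/kg/day (HPEN).

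This rests on Table 1 as printed, on feeds being titrated to calories as written, and on the formula being the source of protein and energy. The 24 h and 72 h figures also assume an uninterrupted ramp. The documents do not support the wider inference that the trial cannot test protein: HPEN vs SEN and HPEN vs PEN both carry a large protein difference.

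**What to change.** 1. Beside Table 1, add protein per 100 kcal (2.54, 2.60, 4.64 g). State that at a shared calorie goal there are two protein levels, and correct the Fig. 2 caption so that it refers to three diets.
2. Keep HPEN vs SEN as the test of Hypothesis 1. Add HPEN vs PEN as a prespecified contrast that better isolates protein.
3. State that PEN vs SEN compares formula and energy density, so that neither a null nor a positive result is read as evidence on moderate protein enrichment, for nitrogen balance or for energy expenditure.
4. Report delivered protein and energy per kg per day by arm at days 1, 3 and 5–7, from the data already registered, to support these readings.

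The feeding rule, arms and sample size do not change. The cost is wording, one table, and multiplicity handling for the added contrast. If the existing Bonferroni correction already covers all three pairwise comparisons, 30 per group still gives 0.84 power for a 0.9 SD difference. The real downside is that PEN vs SEN no longer counts as a protein-dose test.

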Higher protein intake has been associated with early achievement of positive nitrogen balance (NB), a surrogate of PB [19–21], promoting protein anabolism [22]. Moreover, higher protein delivery has been related to lower mortality and higher ventilator-free days in PICU patients [23, 24]. However, the exact and safe amount of protein needed to avoid negative PB remains unclear. Protein intakes greater than 3 g/kg per day have been associated with elevated serum urea nitrogen levels and metabolic acidosis [19, 20, 25, 26], but other studies have reported a higher incidence of lower intelligence quotient in very-low-birth-weight infants receiving over 6 g/kg per day of protein [27, 28].

The aim of the present study is to analyze whether the administration of a high-protein diet improves protein metabolism (serum protein levels and NB) in critically ill infants without increasing energy expenditure assessed by indirect calorimetry. A secondary objective is to register possible secondary effects of the protein-enriched diet.

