### Study ending

The study will be ended:
after 7 days of enteral feeding.at PICU discharge.if hyperproteinemia greater than 8.5 g/dL is present.if serum urea levels exceed 80 mg/dL without evidence of renal function disturbance—in accordance with KDIGO (Kidney Disease Improving Global Outcomes) criteria—or suspected hypercatabolic state (underlying condition and negative nitrogen balance).

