### Study outcomes

The primary outcome of the study will be the variation of NB from baseline to the study ending and the incidence of hyperproteinemia or uremia causing the need to stop the study. Secondary outcomes include the variation of plasma protein levels (total proteins, albumin, prealbumin, transferrin, and RBP), expenditure energy measured by indirect calorimetry, and the incidence of gastrointestinal complications (abdominal distension, vomiting, diarrhea, and excessive gastric residue) and metabolic acidosis.

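### Nitrogen balance has no term for change in body urea, so a greater urea rise in the high-protein arm while balance is measured would be read as protein retained

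*Protocol article*

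**What the plan says.** The section on recruitment, randomization and study development defines the measure: "NB will be calculated as nitrogen intake minus total nitrogen losses". It then lists the losses: "Total nitrogen losses will include total urinary nitrogen and fecal/miscellaneous losses estimated in accordance with the World Health Organization recommendations". Nothing is subtracted for nitrogen that stays in the body as urea. The same section schedules blood urea at admission and at days 1, 3 and 5-7 of feeding, and records weight at inclusion.

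Under Study outcomes, "The primary outcome of the study will be the variation of NB from baseline to the study ending", together with the incidence of hyperproteinemia or uremia that stops the study. The Discussion gives the interpretation: "We will use NB, considering a positive NB as an indicator of protein anabolism and a negative NB as protein catabolism".

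The article also expects urea to respond to protein. In the Background: "Protein intakes greater than 3 g/kg per day have been associated with elevated serum urea nitrogen levels and metabolic acidosis". The third hypothesis, on the two enriched diets, says that "mild gastrointestinal side effects and tolerable serum urea and total protein elevation are adverse events". Under Study ending, one reason to end the study is "if serum urea levels exceed 80 mg/dL without evidence of renal function disturbance", with a further qualifier about a hypercatabolic state.

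**The concern.** Nitrogen taken in and not excreted can go to two places: new protein, or a larger urea pool. Urea nitrogen comes from amino acids that have already been broken down, so a growing pool is not anabolism. Intake minus losses cannot tell the two apart. If urea rises more in one randomised arm, that arm's balance is raised by nitrogen that was catabolised but not yet excreted.

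HPEN is where the article's own statements lead one to expect this. At stake is the first objective, improved protein metabolism: part of an apparent gain in HPEN could be urea accumulation. Better urine collection would not remove the problem, because it remains even with a perfect 24-hour total urinary nitrogen.

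**Working it through.** The article gives no figure for an expected urea change or balance difference, so there is none to reproduce on this point. Its one calculated design figure, 30 per group, does not enter. (It reproduces closely: a two-sided t-test at 0.05/3 with a standardized difference of 0.9 needs 28 per group for 80% power, and 30 per group gives about 84%.)

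**Inputs from the article.** Table 1, per 100 mL: SEN 1.7 g protein and 67 kcal; the protein-enriched diet (PEN) 2.6 g and 100 kcal; HPEN 5.1 g and 110 kcal. Energy target 60-65 kcal/kg/day. Urea limit 80 mg/dL.

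**Assumptions, not in the article.** Nitrogen = protein / 6.25. Urea is distributed in total body water of 0.6-0.7 L/kg. Nitrogen is 28/60 of urea by mass. The between-arm difference in urea change is 20-40 mg/dL, for illustration.

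**Step 1: nitrogen intake at target.** Protein per kg = (protein / kcal) x kcal/kg/day.
- SEN: 1.7/67 x 60 to 65 = 1.52-1.65 g/kg/day, or 244-264 mg N/kg/day.
- PEN: 2.6/100 x 60 to 65 = 1.56-1.69 g/kg/day, or 250-270 mg N/kg/day.
- HPEN: 5.1/110 x 60 to 65 = 2.78-3.01 g/kg/day, or 445-482 mg N/kg/day.

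The HPEN-SEN gap is 201.5 mg N/kg/day at 60 kcal and 218.3 at 65 kcal. PEN and SEN differ by only about 6 mg, so the issue mainly concerns HPEN.

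**Step 2: nitrogen held as urea.** Stored N (mg/kg) = urea change (mg/dL) x 10 x body water (L/kg) x 28/60.
- 20 mg/dL: 200 x 0.6 to 0.7 x 28/60 = 56-65 mg N/kg.
- 40 mg/dL: 400 x 0.6 to 0.7 x 28/60 = 112-131 mg N/kg.

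**Step 3: share of the intake gap.**

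| Between-arm difference | Spread over 3 days | Spread over 5-7 days |
|---|---|---|
| 20 mg/dL | 19-22 mg N/kg/day, 9-11% | 8-13 mg N/kg/day, 4-6% |
| 40 mg/dL | 37-44 mg N/kg/day, 17-22% | 16-26 mg N/kg/day, 7-13% |

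The low ends divide by 218.3 and the high ends by 201.5; for example, 18.7/218.3 = 9% and 43.6/201.5 = 22%.

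**Step 4: what moves these figures.** Some of the extra nitrogen will be excreted, so the balance difference is smaller than the intake gap and the share of it is larger. If half the extra nitrogen is apparently retained (an assumption), then at 0.65 L/kg and a gap of 210 mg, 20 and 40 mg/dL over 3 days come to 19% and 39% of the apparent difference. In the other direction, balance is a daily rate, so only urea change during the measurement period counts. A high but stable urea adds nothing.

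**The case against.** Intake minus losses is the ordinary definition of nitrogen balance. The article calls it a surrogate and says that no method evaluates protein metabolism directly. That stands: the formula is not an error. The weakness lies in reading its sign as anabolism or catabolism while expecting urea to differ by arm.

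Four stronger readings might be inferred, and the article does not support them.
- *The error always inflates balance.* It takes the sign of the urea change. An infant whose urea falls after admission gets a balance that is too low, and only the difference between arms biases the contrast.
- *Harm is hidden as benefit.* Uremia that stops the study is part of the primary outcome, serum urea is a recorded safety variable, and plasma proteins are separate secondary outcomes. The rise would be visible; it would simply not be taken out of the balance.
- *The bias is known to be large.* No rise is stated. The Background ties raised urea nitrogen to intakes above 3 g/kg/day, and HPEN at its energy target is at or just below that level. SEN urea may move too. If urea has settled by days 5-7, the bias in that visit's balance is near zero.
- *The primary outcome should be replaced by a corrected balance.* The first urea is taken at admission, so there is no earlier value with which to correct baseline balance. A between-visit average also does not match a 24-hour or isolated urine sample exactly, and weight is recorded only at inclusion.

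These points limit the size of the problem and the remedy. They do not remove it, because the article neither assumes nor shows that urea is steady when balance is measured, and its urea limit allows for the opposite.

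**Conclusion.** The point holds in a limited form. The stated balance measures protein retention only when urea is steady. A urea rise that is greater in HPEN than in SEN while balance is measured would favour HPEN. Infants stopped for urea above 80 mg/dL are a particular case if their last balance falls while urea is still climbing.

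For an assumed between-arm difference of 20-40 mg/dL, the bias is about 9-22% of the nitrogen intake gap over 3 days and about 4-13% over 5-7 days, and near zero after a plateau. These figures rest on body water of 0.6-0.7 L/kg, the 6.25 factor and feeding at the energy target. The sample size and the PEN-SEN comparison are little affected. What is exposed is the claim that a better balance in HPEN shows anabolism.

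**What to change.** Keep the stated nitrogen balance as the primary measure. Prespecify a supportive analysis of the between-arm contrast, in which each follow-up balance is reduced by the change in body urea nitrogen since the previous visit:

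change in serum urea (mg/dL) x 10 x body water (0.6-0.7 L/kg) x inclusion weight (kg) x 28/60, divided by the days between the two visits, in mg N/day.

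Run it at both ends of the body-water range. State in advance that improved anabolism will be concluded only if the contrast holds with and without the correction. Because the trial is open-label, this should be fixed before the data are examined.

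The cost is small: serum urea and inclusion weight are already collected, so no samples or visits are added. The analysis does need an assumed body water, uses a single weight, and averages the urea change over the visit interval. Baseline balance cannot be corrected, but this does not bias the randomised contrast because baseline is balanced between arms in expectation.
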